### Data collection and analysis

An electronic dataset will be filled (SPSS ver. 20, IBM).

All data will be recorded with paper case report forms and entered electronically at both participating sites using a common dataset. Original study forms will be stored in numerical order and stored in a secure and accessible place for 30 years after study completion. A biostatistician will perform quality control before data analysis, including check for double data entry and range for data values. Missing data will be included in the analysis using specific modern imputation methods.

Statistically significant differences will be determined using Fisher’s exact test, chi-squared test, Student’s t test or the Wilcoxon test, as appropriate.

An interim analysis (315 randomized completed cycles) of clinical pregnancy rates will be performed in order to highlight unforeseen or higher-than-expected effects of vitamin D supplementation. According to the Haybittle–Peto boundary rule, the statistical significance for deciding to stop the trial is set to *p*-value < 0.001 [18]. Results of the interim analysis will be available to all medical and laboratory staff. The steering committee decides on the continuation of the trial and will report to the involved ethics committees.

In accordance with national guidelines, the main outcome will be collected for every woman in order to complete their clinical charts. Since the main outcome is the clinical pregnancy rate as (defined as the presence of at least one intrauterine gestational sac with viable foetus), it has to be noted that its evaluation is highly standardized and fully objective. Moreover, according to legal requirements and standard clinical protocols, secondary outcomes related to the evolution of pregnancies will be easily collected through usual methods and reminders for contacting patients.

Given the study design, protocol adherence is foreseen to be complete. However, data will be analysed according to the “intention to treat” analysis.

Since the clinical trial is designed as minimal risk a formal committee for data monitoring is not foreseen.

Electronic monitoring of the datasets will be performed by two independent physicians every 3 months during recruitment focussing on: completeness of the data, eligibility criteria, date of randomization, treatment assignment, adverse events and endpoints, signed informed consent.

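### The single interim stopping threshold, p < 0.001 on pregnancy rates with no stated direction, is a poor detector of a lower pregnancy rate on vitamin D; a separate non-binding harm guideline would remedy this cheaply

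*Protocol article*

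**What the plan says.** In the protocol article, 'Data collection and analysis' gives the timing and subject of the look: "An interim analysis (315 randomized completed cycles) of clinical pregnancy rates will be performed". Its purpose is stated as "in order to highlight unforeseen or higher-than-expected effects of vitamin D supplementation". The criterion follows, with the Haybittle–Peto rule named as its source: "the statistical significance for deciding to stop the trial is set to" p < 0.001. No sidedness is given, and no other threshold is attached to this look.

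On who decides, the same section states: "The steering committee decides on the continuation of the trial and will report to the involved ethics committees". There is no independent committee: "Since the clinical trial is designed as minimal risk a formal committee for data monitoring is not foreseen". The section also says that interim results will be available to all medical and laboratory staff. Separately, two independent physicians monitor the datasets every 3 months during recruitment; the items listed include treatment assignment, adverse events and endpoints.

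'Sample size calculation' assumes 20% pregnant without supplementation and 30% with it. 'Background' (second hypothesis) names that 10-point gain as the clinically relevant size.

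**The concern.** The purpose has two parts, and the threshold suits only one of them. A Haybittle–Peto boundary is extreme so that an early look spends almost none of the type I error reserved for a claim of benefit. A look for an unforeseen effect in the wrong direction makes no such claim, so it does not need that protection to the same degree.

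Using one threshold for both parts means a substantial loss of pregnancies could be present at the interim without triggering the only numerical rule that the article gives. Leaving the direction open makes this worse. Under one reading harm must be extreme to count, and under the other it cannot count at all. At stake is whether the look can do the second job assigned to it.

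**Working it through.** **Inputs.** 315 completed cycles and p < 0.001 ('Data collection and analysis'); 1:1 allocation ('Randomization'), taken as 157 placebo and 158 vitamin D; 20% and 30%, errors 0.05 and 0.20, chi-squared test ('Sample size calculation'). The two-sided reading is an assumption, for which |z| must exceed 3.29.

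**The plan's own figure.** With a pooled rate of 0.25,

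n = [1.96 × √(2 × 0.25 × 0.75) + 0.8416 × √(0.20 × 0.80 + 0.30 × 0.70)]² / 0.10² = (1.2002 + 0.5119)² / 0.01 = 293.2, so 294 per arm.

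The article says 300. The inflation 600 / (0.90 × 0.95) = 702 agrees with 700. The planned size reproduces.

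**Where harm meets the rule.** Use z = (p_C − p_T) / √[p(1 − p)(1/157 + 1/158)], with p the pooled rate, and 31/157 (19.7%) pregnant on placebo.

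- 11/158 (7.0%) on vitamin D: p = 42/315 = 0.1333; SE = 0.0383; z = 0.1278/0.0383 = 3.34; two-sided p = 0.00085 (Fisher 0.00086). The rule is met.
- 12/158 (7.6%): p = 43/315 = 0.1365; SE = 0.0387; z = 0.1215/0.0387 = 3.14; p = 0.0017. The rule is missed.

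So 11 is the largest count that qualifies, a relative fall of 1 − 0.0696/0.1975 = 65%. Across chi-squared (with and without continuity correction) and Fisher's test, the fall needed is about 64–69%. If 0.001 were applied one-sided towards harm, the limit would be 12/157 (7.6%), a fall of about 62%.

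**Dependence on the placebo rate.** The relative fall needed shrinks as the placebo rate rises:

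| Placebo rate | Fall needed (range over tests) | Example (chi-squared) |
|---|---|---|
| 15% | 75–79% | 24/157 v 6/158 |
| 20% | 64–69% | 31/157 v 11/158 |
| 25% | 57–60% | 39/157 v 16/158 |
| 30% | 51–55% | 47/157 v 22/158 |
| 40% | 43–46% | 63/157 v 36/158 |

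**Chance of meeting the rule for harm.** A normal approximation for true rates of 20% v 10% gives SE under the null = √[0.15 × 0.85 × (1/157 + 1/158)] = 0.0402 and SE under the alternative = √(0.16/157 + 0.09/158) = 0.0399.

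- p < 0.001: Φ[(0.10 − 3.29 × 0.0402)/0.0399] = Φ(−0.81) = 0.21.
- One-sided 0.025: Φ[(0.10 − 1.96 × 0.0402)/0.0399] = Φ(0.53) = 0.70.

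Exact binomial enumeration with the pooled z test, placebo rate 20%, gives the following (where two values appear, they are the two ways of splitting 157/158):

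| True rate on vitamin D | P(two-sided p < 0.001, harm side) | P(one-sided p < 0.025) |
|---|---|---|
| 20% (no effect) | 0.0005 | 0.025 |
| 15% | 0.015–0.016 | 0.21 |
| 10% | 0.20–0.21 | 0.71 |
| 7% | 0.54–0.55 | 0.93–0.94 |

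A 10-point loss from 20% would therefore miss the stated threshold about four times in five. With 31/157 on placebo, the one-sided 0.025 guideline would be met at 18/158 (11.4%) or fewer.

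**The case against.** The strongest reply is that a symmetric boundary is a legitimate design choice and contradicts nothing in the article. Stopping on a chance adverse trend would also cost the trial its answer, so some strictness towards harm can be defended. That is fair, and it is why the guideline proposed here prompts a review and does not bind.

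A second reply is that 20% against 71% is not like for like: the first is the chance of meeting a stopping threshold, the second the chance of prompting a review. The steering committee already decides on continuation at this look and may weigh an adverse trend that falls short of p < 0.001. This also stands. The gain is a formal trigger, not 51 percentage points of protection. In addition, a halving of the pregnancy rate is a scenario and not a prediction; the evidence cited in 'Background' is an association favouring vitamin D and one small trial without benefit.

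A reader might infer more: that adverse events never reach the stopping decision, or that this is the only look that can stop the trial. The article supports neither. Its 3-monthly review covers treatment assignment, adverse events and endpoints, and nothing bars the steering committee from acting on it. The article does not state a reporting line or an adverse-event criterion, but a condensed article may leave those to the full protocol, so their absence is not part of this point. A reader might also argue that most women would already have been dosed by the time of the look. That depends on an accrual period that the article does not give, counts women on placebo, and applies to any mid-trial look.

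**Conclusion.** The point holds in a limited form. The article fixes one threshold, without a direction, for a look that is meant to reveal unforeseen effects as well as large benefit. On the two-sided reading, at a 20% placebo rate, the rule needs a fall to about 7% and would register a true 10-point loss about one time in five. On a benefit-only reading it would never register harm. The wording of the purpose favours the two-sided reading but does not settle it.

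The result rests on an even split of the 315 cycles, the protocol's 20% placebo rate and a pooled chi-squared test. Fisher's test gives the same limit at 20%, and a continuity correction moves it by one event. The figure of about two thirds should not be quoted without the 20% condition. The finding is an inexpensive improvement to a stated rule and does not invalidate the trial's final analysis.

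**What to change.** Amend the interim paragraph in three respects.

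1. State the sidedness of the p < 0.001 criterion, and keep it as the threshold for stopping for benefit.
2. Add a separate, explicitly non-binding guideline for a lower pregnancy rate on vitamin D. For example, one-sided p < 0.025 at the same look prompts a formal steering committee review of whether to continue.
3. Provide that any comparison by arm used for this goes only to those who decide on continuation. As written, interim results go to all medical and laboratory staff, while 'Blinding' requires caregivers and embryologists to be blinded, so the guideline should not be run through that open report.

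The cost is a few lines of amendment and restricted circulation of one analysis. If vitamin D has no effect, there is about a 2.5% chance of a review that was not needed. The type I error for superiority is not inflated: the guideline gives no new opportunity to claim benefit, and stopping after a review could only reduce the chance of such a claim.

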### Blinding

All patients, all caregivers and embryologists at the clinical departments will be blinded to trial intervention allocation. This is possible because ampoules of drug/placebo will be prepared and coded in a undistinguishable way by the local central pharmacy of the Fondazione IRCCS Ca′ Granda according to a computer generated random list. The pharmacy will reveal the content of administered ampoule only after cycle completion.

The allocation sequence will be implemented through administration of anonymized ampoules in the progressive order they are coded by the pharmacy.

The progress of the study will be periodically monitored by an external monitor in order to verify the strictness of the data management. The medical doctors evaluating the main outcome will also be blinded to the trial intervention allocation. Unblinding will be possible after the embryo transfer procedure. In case of adverse effects of vitamin D supplementation, as reported by participating women, the care giver of the patient can obtain information on the participant’s allocated intervention asking to the principal investigator who will ask the pharmacy using a specific module.

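### Interim results on the primary outcome go to all medical and laboratory staff while about half the trial is still to run, which undermines the purpose of the double blind

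*Protocol article*

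**What the plan says.** All of the interim provisions are in the Protocol article, *Data collection and analysis*:

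- The look is on the primary outcome: "An interim analysis (315 randomized completed cycles) of clinical pregnancy rates will be performed".
- Its purpose is comparative: "in order to highlight unforeseen or higher-than-expected effects of vitamin D supplementation".
- It has a formal boundary (Haybittle–Peto): "the statistical significance for deciding to stop the trial is set to" p < 0.001.
- The results are distributed: "Results of the interim analysis will be available to all medical and laboratory staff".
- On the decision: "The steering committee decides on the continuation of the trial and will report to the involved ethics committees".
- On oversight: "a formal committee for data monitoring is not foreseen".
- A separate data check exists: "Electronic monitoring of the datasets will be performed by two independent physicians every 3 months during recruitment". Its listed content includes treatment assignment and endpoints.

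The *Blinding* section says "All patients, all caregivers and embryologists at the clinical departments will be blinded to trial intervention allocation", and extends this to the doctors who assess the main outcome. It also lets the pharmacy disclose the ampoule content once the cycle is complete, and permits unblinding after embryo transfer. *Experimental design aim 1* counts thawed transfers toward the outcome if they take place within 4 months of retrieval. It also relies on staff being unaware of vitamin D levels to argue that the study will not influence how stimulation is managed.

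**The concern.** This is a stated rule, not a detail left to another document. A fuller protocol or an analysis plan could not cure it without contradicting the published sentence. Nothing in the article limits the release to a stop/continue message, delays it to the end of the trial, or separates those who see the comparison from those who treat the women.

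The people who receive the results invite women into the trial, keep them in it, and ask them not to take further vitamin D. After a favourable trend they may discourage some women from joining or be less firm about outside vitamin D. After a flat trend, effort on recruitment and retention may slacken. The likely results are a diluted contrast, lost power, and a final result that is harder to defend. Once the figures are known at the sites, no analysis can undo it.

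The individual unblinding rules add to this. If a woman's arm can be disclosed after her cycle or transfer, staff can build up results by arm themselves. If disclosure may follow the fresh transfer, they could know both the interim trend and her arm while a thawed transfer could still count.

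**Working it through.** **1. Reproduce the plan's sample size.** Inputs from *Sample size calculation*: 20% versus 30%, type I error 0.05 (taken as two-sided), power 0.80, chi-squared test.

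n per arm = [1.960 × √(2 × 0.25 × 0.75) + 0.842 × √(0.20 × 0.80 + 0.30 × 0.70)]² / 0.10² = 293.2, so 294.

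The plan uses 300. With 300 per arm, power = Φ[(√300 × 0.10 − 1.960 × 0.6124) / 0.6083] = Φ(0.874) = 80.9%. The plan's figure reproduces.

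**2. How much of the trial follows the look.**

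| Base | Interim share | Still to complete |
|---|---|---|
| 600 required | 315/600 = 52.5% | 285 (47.5%) |
| 630 randomised (700 × 0.90) | 315/630 = 50.0% | 315 (50.0%) |

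The trigger counts completed cycles, so some of these women will already be randomised and dosed when results are released. The share still to be recruited is therefore somewhat below half, but informed staff would manage all the remaining cycles.

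**3. Would the trial continue?** There are about 157.5 women per arm at the look, and two-sided p < 0.001 gives a critical value of 3.29.

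- Standard error of the difference at a mean rate of 25%: √(2 × 0.25 × 0.75 / 157.5) = 0.0488.
- Difference needed to stop: 3.29 × 0.0488 = 0.161, about 16 percentage points.
- 95% half-width: 1.96 × 0.0488 = 0.096, about 9.6 points.
- Chance of stopping if 20% versus 30% is true: Φ[(√157.5 × 0.10 − 3.29 × 0.6124) / 0.6083] = Φ(−1.25) = about 11%.

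So in roughly nine cases out of ten the trial goes on with the results known, even if the planned effect is real. What staff would hold is an estimate almost as uncertain as the 10-point effect the trial seeks.

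**4. Type I error.** With p < 0.001 at the look and 0.05 at the end, overall type I error is about 0.0502. The issue is trial conduct, not alpha.

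**5. Illustration of dilution.** Assumptions, not in the protocol: half of the placebo women come after the look; a fraction u of them take vitamin D; this gives a fraction e of the full 10-point benefit. Placebo rate = 20% + 0.5 × u × e × 10 points. Power is at 300 per arm against 30%.

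| Uptake u | Placebo rate, half effect | Power | Placebo rate, full effect | Power |
|---|---|---|---|---|
| 10% | 20.25% | 78.8% | 20.5% | 76.5% |
| 20% | 20.5% | 76.5% | 21.0% | 71.6% |
| 30% | 20.75% | 74.1% | 21.5% | 66.4% |

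**The case against.** The strongest reply is that the blind in this protocol concerns each woman's allocation, and an aggregate result does not disclose it. Ampoules are coded and indistinguishable, the central pharmacy holds the list, and outcome assessors are blinded. This stands. A reader might infer that releasing the interim results defeats the blinding, but the documents do not support that: no woman still in cycle is unmasked by the sentence in *Data collection and analysis*.

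A reader might also infer that a positive final result could be an artefact of the release. That too goes beyond the documents. While allocation is hidden, a change in whom staff invite, how they grade embryos or how actively they pursue a thawed transfer falls on both arms alike. The randomised comparison within each period stays valid. Outside vitamin D would also reach both arms, and would mainly shrink the difference.

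Three further points carry some weight.

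- The protocol regards the outcome as standardised and objective. That limits assessment bias, but does not protect recruitment, retention or adherence to the request to avoid vitamin D.
- That same request makes heavy outside use less likely, and the protocol gives no basis for any uptake rate, so the power figures are illustrative only.
- The sentence does not say that results are shown by arm. This is an inference, but a safe one: a test of the effect of vitamin D on pregnancy rates against a p-value boundary has to compare arms.

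The protocol's minimal-risk argument for having no monitoring committee concerns safety oversight. It does not answer the question of confidentiality.

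**Conclusion.** The concern holds in this form: the protocol releases a comparative interim result on its primary outcome to the staff who run the trial, at 50% to 52.5% of the sample, when continuation is by far the likeliest course. This undermines what the double blind is for, without breaking the allocation of women still in cycle.

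The supportable consequences are dilution, lost power and lost credibility, not demonstrated bias in favour of vitamin D and not inflated type I error. The power loss, from 80.9% to somewhere between 78.8% and 66.4%, depends wholly on the assumed uptake and effect of vitamin D outside the trial.

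The individual unblinding rules make the exposure worse. The *Blinding* section does not say whether cycle completion or embryo transfer covers later thawed transfers. If it does not, a woman's arm could be known while her outcome is still open.

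**What to change.** **In *Data collection and analysis***, replace the sentence on availability of the interim results with text to this effect: comparative interim results are seen only by the biostatistician and the two independent physicians already named for data monitoring; they give the steering committee a recommendation to continue or stop; no comparative result reaches the steering committee, site staff or laboratory staff before database lock unless the boundary is crossed. State that the two physicians' role is extended to this task, since at present it covers data checks only.

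**In *Blinding***, state that allocation is not revealed to site staff before database lock, apart from the existing route for adverse effects, which stays as it is. Without this second change, sites could still assemble results by arm themselves.

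**Cost:** two short paragraphs in one amendment. The boundary, the sample size and the steering committee's authority are unchanged. The roles already exist, although the two physicians would have to accept the added task. The steering committee would act on a recommendation rather than on the data, and women and staff would learn the allocation later.

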### Sample size calculation

The sample size was calculated according to Kane [19] based on the following assumptions:

1) the primary outcome is the cumulative clinical pregnancy rate (CPR) per started cycle; 2) expected CPR in the deficient population 20% [7], 3) expected CPR in the supplemented population 30% [7], 4) expected proportion of women with insufficient serum vitamin D (< 30 ng/ml): 90% [20], 5) Type I and II errors of 0.05 and 0.20, respectively. Under these assumptions, a sample size of 300 randomized women per arm will allow us to detect with sufficient statistical power (*p* < 0.05) an absolute difference ≥ 10% in the CPR rate between the two groups using the chi-squared test.

Considering that 10% of recruited women are expected to have serum vitamin D levels ≥30 ng/ml (therefore they will not be randomized) and considering a dropout rate of 5%, it has been decided to recruit 700 women to reach the number of 600 required subjects. The full formula used for sample size calculation is provided as an additional figure (see Additional file 2).

### Randomization

Randomization will be organized centrally by UOC Farmacia of the Fondazione IRCCS Ospedale Maggiore Policlinico. The allocation sequence will be computer-generated and hidden from the participants as well as from the physicians and biologists involved in the clinical management of the patients. The allocation ratio will be 1:1. Randomization list will be stratified for the two participating centres. Since the random list has not other stratification, the allocation sequence is considered unpredictable and no restrictions are planned in order to reduce predictability.

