## Background

Vitamin D plays an important role in human physiology and pathology. The activation of the vitamin D receptor (VDR) may regulate directly and/or indirectly the expression of a very large number of genes (0.5–5% of the total human genome). Accordingly, vitamin D insufficiency has been shown to increase the risk of several diseases including cancers, auto-immune diseases, infections and pregnancy complications [1, 2].

In recent years, a role of vitamin D has been also postulated in reproductive health. VDR is expressed in the ovary, the endometrium and the myometrium [3]. Moreover, vitamin D has been shown to influence female fertility potential in animals and humans [4, 5]. In vitro fertilization (IVF) success was demonstrated to be higher in women with appropriate reserves of vitamin D [6]. In a recent contribution from our group, we detected an adjusted odds ratio (a-OR) (adjusted for age, ethnicity, BMI, parity, duration of infertility, number of retrieved oocytes, number of transferred embryos, and study period) of 2.15 [95% confidence interval (CI): 1.23–3.77] for clinical pregnancy rate in women with vitamin D > 20 ng/ml compared to those with vitamin D < 20 ng/ml. A similar figure was observed when considering the implantation rate. Of note, this beneficial effect was even more evident when using a threshold of 30 ng/ml [7]. The large body of evidence available in animal models and data from in vitro studies in women strongly favour a causal relation, but evidence from RCTs is required to definitely support a role for vitamin D in influencing the chances of pregnancy. To date, only a small RCT has been published and no benefits emerged [8]. However, the study was insufficiently powered to draw definite conclusions (in total 117 women). Moreover, only women scheduled for frozen embryo transfer were included.

Exploring the mechanisms at the basis of the beneficial effects of vitamin D could also be relevant and may open new avenues of research. To date, there are few appealing findings but the scenario is incomplete, especially from interventional studies. Biological evidence from RCTs could conversely provide crucial insights on the role of vitamin D in influencing oocytes quality or endometrial receptivity.

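### Centre stratification without restriction balances nothing, and the unadjusted primary test leaves a modest, nearly free gain in precision unused

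*Protocol article*

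**What the plan says.** Randomization section, Protocol article: "Randomization list will be stratified for the two participating centres". The allocation ratio is 1:1. The same paragraph argues that, because the list has no further stratification, the sequence is unpredictable, and it adds that "no restrictions are planned in order to reduce predictability".

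The Sample size calculation section plans to detect a difference of at least 10 percentage points "in the CPR rate between the two groups using the chi-squared test". The Data collection and analysis section names Fisher's exact, chi-squared, Student's t and Wilcoxon tests, to be chosen as suits the variable. Neither section gives centre or any baseline variable a role in the comparison.

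The Background section cites the group's earlier odds ratio, which was "adjusted for age, ethnicity, BMI, parity, duration of infertility, number of retrieved oocytes, number of transferred embryos, and study period".

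The Blinding section says that coded ampoules are given in sequence and that the pharmacy discloses an ampoule's content once that woman's cycle is complete.

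**The concern.** Stratifying a list improves balance only if the sequence within each stratum is restricted, usually by permuted blocks. Two unrestricted lists, one per centre, produce the same spread of imbalances as a single unrestricted list. On the plain reading, the protocol therefore names a design feature that does nothing.

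The rationale is also a non sequitur. The absence of further strata does not make a sequence unpredictable. Concealment here comes from central generation by the pharmacy and from indistinguishable coded ampoules; an unrestricted sequence adds unpredictability of its own.

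On the analysis side, centre is the only factor the randomisation uses, yet no named test uses it. Age, AMH, number of previous attempts and serum 25(OH)D are all established before randomisation, because eligibility depends on them (Participants section). The trial is planned at 80% power with little margin, so what is at stake is precision obtainable without recruiting anyone else.

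**Working it through.** **Inputs.** From the Sample size calculation section: "Type I and II errors of 0.05 and 0.20, respectively"; pregnancy rates of 20% and 30%; "a sample size of 300 randomized women per arm"; 10% not randomised because they are vitamin D sufficient; 5% dropout. From the Abstract: 700 women split equally between two centres. Sidedness is not stated; two-sided is assumed.

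**1. The plan's own figures.** With a pooled variance and no continuity correction:

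n per arm = [1.96·√(2·0.25·0.75) + 0.8416·√(0.2·0.8 + 0.3·0.7)]² / 0.10² = (1.2003 + 0.5119)² / 0.01 ≈ 293.2, so 294.

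Power at 300 per arm is 80.9%. Recruitment: 600 / (0.90 × 0.95) = 702, against 700 stated. Both figures reproduce.

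**2. Balance within a centre under unrestricted 1:1 allocation.** If X of n women receive vitamin D, X is Binomial(n, 0.5). The arm difference is 2X − n, with SD √n.

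| Women per centre | Source | SD of difference | 95% range of one arm |
|---|---|---|---|
| 300 | 600 / 2 | 17.3 | 133 to 167 |
| 315 | 700 × 0.90 / 2 | 17.7 | 140 to 175 |

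With 300 women, a difference of 20 or more has a 27% chance and one of 30 or more a 9% chance. With 315, a split of 45:55 or worse has about a 7% chance. These figures are identical with and without stratification. Blocks of 4 within centre would cap the difference at 2.

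**3. What the imbalance costs.** Power of the chi-squared test with 600 women in total:

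- 300 v 300: 80.9%
- 276 v 324 (edge of the 95% range): 80.5%
- averaged over all splits: 80.8%

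The average loss is about 0.1 point.

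**4. What using centre gains.** The simulation had 4,000 runs, 600 women and simple allocation, and compared crude chi-squared with Cochran-Mantel-Haenszel by centre. The documents do not give the difference in pregnancy rate between centres, so it is varied.

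| Assumed centre difference | Crude | By centre |
|---|---|---|
| 0 points | 80.5% | 80.8% |
| 5 points | 80.8% | 80.6% |
| 10 points | 81.8% | 82.0% |
| 15 points | 81.9% | 82.8% |

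The gain is 0 to about 1 point, with a Monte Carlo error of about 0.6 point per figure.

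**5. What using baseline covariates gains.** The simulation had 2,500 runs and compared crude chi-squared with logistic regression on treatment and one standardised baseline score. The score's strength is an assumption.

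| Log odds ratio per SD (AUC) | Crude | Adjusted | Gain |
|---|---|---|---|
| 0.3 (0.58) | 80.7% | 80.9% | 0.2 |
| 0.5 (0.64) | 81.9% | 83.0% | 1.0 |
| 0.8 (0.70) | 81.8% | 85.5% | 3.7 |
| 1.0 (0.74) | 81.6% | 86.7% | 5.1 |

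The Monte Carlo error is about 0.8 point per figure. As a cross-check, power ≈ Φ(0.10 / √[(0.16 + 0.21)/300 · (1 − R²)] − 1.96). The strongest score has R² = 0.133, which gives 86.4%; R² = 0 gives 81.3%.

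**6. Validity.** Under no effect, the crude test rejected in about 4% to 6% of runs in every scenario.

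**The case against.** The strongest reply is that almost nothing is lost. If allocation is in effect simple 1:1, the unadjusted chi-squared test matches the design and ignoring centre is no error. The covariate gain depends on an assumed strength, and the entry limits (age 18 to 39, AMH not below 0.5 ng/ml, fewer than 3 attempts, 25(OH)D below 30 ng/ml) narrow the predictors and may push the gain towards the low end. All of this stands, and it limits the point to efficiency and clarity.

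Blocking also has a cost. With ampoules used in sequence and contents disclosed after each cycle, staff could infer blocks while recruitment is still open. Under that arrangement an unrestricted list is the less predictable choice. The protocol's choice is therefore defensible, though the reason it gives is not the right one. Blocking within centre would not correct a chance imbalance in age either.

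The sentence on restrictions is awkward. It could mean that no further measures against predictability are planned, rather than that there are no blocks. That stands as well, and the wording needs clarifying on either reading.

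A reader might infer that the Background model commits the group to adjustment. It does not. That model addressed confounding in observational data. Of the covariates proposed here it shares only age, and its retrieved-oocyte and transferred-embryo terms arise after randomisation.

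Finally, covariate lists are commonly left to an analysis plan, which is not shown. For that reason the point is not that an adjusted model is missing. It is that the method the protocol does name for sizing the primary comparison can be improved at almost no cost.

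**Conclusion.** On the plain reading of the Randomization section, stratification by centre gives no balance and the rationale for unpredictability does not follow. The named primary comparison is valid but gives up some precision: about 0 to 1 point of power for centre (assumed centre differences of 0 to 15 points) and about 0 to 5 points for baseline covariates (assumed AUC of 0.58 to 0.74). The imbalance itself costs about 0.1 point.

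A reader who sees possible splits such as 140 v 175 might infer that the trial is biased or materially underpowered. The figures do not support that: type I error holds, and power stays at 80.5% even at the edge of the 95% range for the overall split. This is a free improvement with a modest gain, not a validity error.

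**What to change.** **Analysis (Data collection and analysis; Sample size calculation).** Prespecify the primary analysis as a logistic model with treatment, centre, age, AMH, previous IVF attempts and baseline 25(OH)D, with no post-randomisation variables. Report it as a standardised risk difference with a 95% CI. This keeps the 10-point absolute scale on which the trial was sized and avoids the gap between conditional and crude odds ratios. At minimum, use a Cochran-Mantel-Haenszel test by centre. Keep the crude chi-squared test as a sensitivity analysis. The sample size need not change.

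**Randomization.** State whether the list within each centre is blocked. Replace the rationale with the actual basis of concealment: central generation and indistinguishable coded ampoules. If blocks are used, vary their sizes randomly, keep the sizes undisclosed outside the pharmacy, and do not release individual allocations routinely while recruitment continues. The provision for unblinding after adverse effects is not affected.

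**Cost.** The analysis change is wording only, since the covariates are already collected for eligibility. Introducing blocks would need a new list for ampoules not yet coded, and the routine disclosure after each cycle would have to wait.
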